	**Qualitative data**					
**Patient**	‘Resources’ and ‘Conversion factors’ (capability approach)	Questionnaire on resources and personal characteristics (self-developed)	x	x		
	Delivery of care in terms of capability approach	Interview on experiences with provided care (audio-recorded)		x		
**Partner (if possible)**	Delivery of care in terms of capability approach	Interview on experiences with provided care (audio-recorded)		x		
**Other**	Delivery of care in terms of capability approach	Audio recordings of consultations with the healthcare professionals			x	
	Delivery of care in terms of capability approach	Audio recordings of multidisciplinary team meetings (audio-recorded)			x	
	Delivery of care in terms of capability approach	Medical records			x	
	Delivery of care in terms of capability approach	Focus groups with healthcare professionals on their experience with providing capability care (audio-recorded)				x

### Sample size calculation

The primary outcome measure is the COPM, which consists of the performance score (COPM-P) and satisfaction score (COPM-S). Both COPM-P and COPM-S scores at 6 months after baseline (T1), corrected for the value at baseline (T0), will be used. We consider the intervention as successful only if for both outcomes the capability care group performs significantly better than the usual care group.

The expected difference between both groups is 1.4 for COPM-P and 1.9 for COPM-S. These values represent a clinically relevant improvement as perceived by the client [19]. The standard deviations in both groups and for both outcomes are expected to be 1.9 at time T1 [20]. Based on these assumptions, a sample size of at least 24 patients per group will yield a power of 80% to show a statistical difference between the intervention and the usual care group at a significance level of 0.05. These calculations are based on ANCOVA-models with the outcome at 6 months as dependent variables, corrected for the value at baseline and an assumed correlation of 0.5 between the outcome values at T0 and T1 [29]. Considering dropout, we decided to include 30 participants in each group.

### Statistical analysis

#### Primary and secondary outcome measures

The primary outcome measure will be analysed using an ANCOVA model with the follow up scores (T1) as dependent variable. Covariates will be the T0 scores, age, gender and diagnosis. For an intervention-effect to be present, the scores on both the COPM-P and COPM-S will need to show a significant change. A p-value below 0.05 will be considered significant.

Similar analyses (ANCOVA model) will be performed for these secondary outcome measures: ICECAP-A preference-weighted index score, ICECAP-A non-weighted sum score, USER-P, CSWQ total score, EQ-5D-5L preference-weighted index score, EQ-5D-5L non-weighted sum score, SF-36 preference-weighted index score, SF-36 non-weighted sum score. The CSWQ overall question will be analysed using a Mann-Whitney U test on the difference score between T0 and T1. A p-value below 0.05 will be considered significant.

To compare the capability measure (ICECAP-A) with the health-related quality of life measures (EQ-5D-5L, SF-36), multiple contingency tables will be created to compare the number of patients that show significant changes in their well-being based on the ICECAP-A, EQ-5D-5L and SF-36 ANCOVA models. These comparisons will be performed both for the sum scores and the preference-weighted scores (i.e. based on utility estimates derived from members of the general population). An analysis solely based on the preference-weighted scores may conclude that the measure is not responsive, when in fact, it could be that the descriptive system of the measure is responsive but the change is not valued [30].

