## Introduction

Facioscapulohumeral muscular dystrophy (FSHD) type 1 and type 2, and myotonic dystrophy type 1 (DM1) both are slowly progressive and among the most prevalent inherited neuromuscular diseases (NMD) [1, 2]. Disease course and severity are highly variable, even within families. There is no curative treatment available for FSHD and DM1. Therefore, treatment of these patients, each with their individual phenotype, requires a personalised rehabilitation approach that focuses on achieving and maintaining a level of functioning that enables them to lead a satisfying life.

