### Study design

#### Patient groups

Two patient groups are included in a controlled before and after design, and the impact of care on their well-being is assessed by using a mixed methods approach. The first group (n = 30) will be included during a period of 6 months, and they will receive usual multidisciplinary outpatient rehabilitation care. The observations made during usual care will be used to inform the development of capability care (as described below). Then, during a period of 3 months, members of the multidisciplinary outpatient rehabilitation care team of the Radboudumc Center of Expertise for neuromuscular disorders will be trained in providing capability care. Subsequently, the second group (n = 30) will be included during a period of 6 months, and they will receive multidisciplinary outpatient rehabilitation capability care. Both groups are followed up for a period of 6 months after inclusion. A schematic illustration of the study design can be seen in the flowchart below (Fig 3). Only patients are blinded with respect to the assignment into the usual care or capability care group.

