### Outcome measures

The primary objective of this study is to assess the impact of capability care on the well-being of patients with NMD. To be able to do this, a set of quantitative outcome measures is used to evaluate and compare different impacts of rehabilitation care on patients with NMD. Additionally, qualitative data is used to perform a process evaluation, providing insight in contextual factors, mechanisms of impact, and a deeper understanding of the impact of care on the daily life of patients.

The primary outcome is the difference in the COPM performance and satisfaction scores between both groups (corrected for the value at baseline) [14]. The COPM is a semi-structured interview designed to help patients identify daily occupations that are meaningful to them and difficult for them to perform. Patients are asked to prioritize 3 to 5 important occupations they would like to improve, for which a score is given for performance from 1 (impossible) to 10 (very well possible) and for satisfaction with performance from 1 (not satisfied) to 10 (extremely satisfied). The COPM is a reliable and valid instrument [15–17], and has been shown to be a sensitive and clinically relevant outcome measure in a number of rehabilitation studies [15, 18–22]. The COPM results are also noted in the patient file, visible for the healthcare team (so that the occupational therapist does not need to repeat the COPM, as this is often used in clinical practice).

Secondary measures include the ICEpop CAPability measure for Adults (ICECAP-A) [23], Utrecht Scale for Evaluation of Rehabilitation Participation (USER-P) [24], EuroQol-5D (EQ-5D-5L) [25, 26], Medical Outcome Study Short Form-36 (SF-36) [27] and the Capability Set for Work Questionnaire (CSWQ) [28]. This broad range of measures provides a way to uncover the diverse impact of care, and to compare the validity of different instruments.

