The qualitative data collection includes a (self-developed) questionnaire on resources and personal characteristics, interviews with participating patients and their partners, audio-recordings of consultations between patients and healthcare professionals, audio-recordings of healthcare professionals’ team meetings, medical records, and focus groups with healthcare professionals after both groups have completed their treatment. The data from the usual care group will be used to develop the capability care intervention (as described above); the data from both groups and the focus groups with healthcare professionals will be used to perform a process evaluation (as described above, Fig 4).

Table 2 provides an overview of all data collection methods.

**Table 2 pone.0261475.t002:** Methods of data collection.

Participant	Outcome	Data collection method	Baseline (T0)	6 months (T1)	Random selection	End of follow-up
**Patient**	**Primary**					
	Performance on and satisfaction with meaningful daily occupations	Canadian Occupational Performance Measure (COPM)–performance and satisfaction score (16)	x	x		
**Patient**	**Secondary**					
	Capabilities	ICEpop CAPability measure for Adults (ICECAP-A) (25)	x	x		
	Participation	Utrecht Scale for Evaluation of Rehabilitation Participation (USER-P) (26)	x	x		
	Health-related quality of life	EuroQol-5D (EQ-5D-5L) (27, 28)	x	x		
	Health-related quality of life	Medical Outcome Study Short Form-36 (SF-36) (29)	x	x		
	Work capabilities	Capability Set for Work Questionnaire (CSWQ) (30)	x	x		

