With respect to challenges related to developing capability care, we have chosen to use a controlled before-after design. We have both pragmatic and methodological reasons for choosing this approach. Because the healthcare team providing specialized care to NMD patients at Radboudumc is too small to divide into two groups (providing usual or capability care) it is not possible to randomly assign the patients to a treatment group (as in a randomized controlled trial). And due to the nature of capability care training, it is also not possible for a professional trained in capability care to provide capability care to one patient and usual care to the other. Professionals will be trained to look at the patient from a different perspective, and after being trained it is not realistic to argue that the professional can let go of this perspective. Besides these pragmatic reasons, the before-after design allows us to learn from the usual care group to be able to develop capability care. An analysis of the qualitative data of usual care can serve as input for discussions with other experts from the capability approach domain and the rehabilitation field on which capabilities are relevant to the well-being of NMD patients and how they could be realized in capability care.

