The current study includes both patients with FSHD and DM1, which involves a high heterogeneity between participants. Although this could increase the complexity of the analyses, we have several reasons for including patients with both types of NMD. The Radboudumc is a (inter)national centre of expertise for both diseases and can provide excellent care for these patients. Both diseases are chronic degenerative NMD with a slowly progressive character, and disease course and symptoms not only show a high variability between NMD but also within patient groups with the same NMD diagnosis. Despite this variation, an important commonality between both diseases is that patients struggle to maintain a level of functioning that leads to a fulfilling life. This matches the goal of rehabilitation treatment to support patients in finding a way to achieve and maintain this level of functioning, leading to a higher well-being. In addition, rehabilitation treatment is always individualized and depends on the patient’s situation, wishes and aims. Therefore, although the treatment is adjusted to personal differences, we do not expect a difference in the comparative effectiveness of usual care and capability care between both diseases. However, to be certain, we decided to analyse our data using diagnosis as a covariate to take the possibility of differences into account.

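### The primary COPM models compare two sequential, non-randomised groups without a T0 health- or functional-status covariate, which may leave residual confounding in either direction

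*Protocol article*

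**What the plan says.** Under Study design (Patient groups) the protocol article states: "Two patient groups are included in a controlled before and after design". Thirty patients receive usual care. After a training period, another 30 receive capability care at the same centre. The Discussion explains that, with one small care team, "it is not possible to randomly assign the patients to a treatment group".

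The model is set out in the Statistical analysis section, under the heading on primary and secondary outcomes, in these words: "The primary outcome measure will be analysed using an ANCOVA model with the follow up scores (T1) as dependent variable". The next sentence fixes the adjustment: "Covariates will be the T0 scores, age, gender and diagnosis". The article describes no matching, weighting or other adjustment for differences between the groups.

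On heterogeneity, the Introduction says: "Disease course and severity are highly variable, even within families". The Discussion says that "disease course and symptoms not only show a high variability between NMD but also within patient groups with the same NMD diagnosis", and answers this with diagnosis as a covariate.

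Under Outcome measures, the COPM is described as an interview "designed to help patients identify daily occupations that are meaningful to them and difficult for them to perform". Patients score three to five such occupations. Table 2 lists EQ-5D-5L, SF-36 and USER-P at T0 and T1, and the Measurements section says that both groups undergo the same measurements. The analysis section uses these instruments only in analyses of themselves.

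**The concern.** Without randomisation, the care effect is the group coefficient that remains after the listed covariates. Two of the four might be expected to represent how severely a patient is affected, and each has a limit that the protocol itself supplies.

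- **Diagnosis** separates FSHD from DM1, but the protocol says that variation within a diagnosis is high.
- **T0 COPM** is scored on occupations chosen because they are difficult for that patient. A mildly and a severely affected patient can both start low, so it need not track general function closely.

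If general functional status predicts the 6-month COPM beyond these covariates, and the two groups differ in it, part of that difference enters the estimated care effect. Both COPM scores could move the same way, because both come from the same patients and the same occupations. At stake is the size of the primary estimate and, less often, the success conclusion. A prognostic T0 covariate would also reduce residual variance.

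**Working it through.** **Inputs from the protocol (Sample size calculation).** Expected differences 1.4 (COPM-P) and 1.9 (COPM-S); SD at T1 1.9; T0–T1 correlation 0.5; significance level 0.05 (taken as two-sided); power 80%; at least 24 per group, raised to 30 for dropout.

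**Step 1. The plan's own figure.** Residual SD = 1.9 × √(1 − 0.5²) = 1.645. For COPM-P, n per group = 2 × (1.960 + 0.842)² × 1.645² / 1.4² = 21.7, so 22. With the noncentral t distribution, 23 per group gives power 0.805 and 24 gives 0.822. The stated 24 is reproduced closely enough, and the sample size is not at issue.

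**Step 2. Standard error.** At 24 per group, SE = 1.645 × √(2/24) = 0.475. At 30 per group, it is 1.645 × √(2/30) = 0.425.

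**Step 3. Bias from an omitted status score.** Bias = d × r × 1.645. Here d is the group difference in status not explained by the existing covariates, in SD units, and r is its partial correlation with T1. Neither is in the documents; the ranges below are assumptions.

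| d | r | Bias (points) | In SE (24 per group) | Share of 1.4 |
|---|---|---|---|---|
| 0.3 | 0.2 | 0.10 | 0.21 | 7% |
| 0.5 | 0.3 | 0.25 | 0.52 | 18% |
| 0.5 | 0.4 | 0.33 | 0.69 | 24% |

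At 30 per group the bias in points is unchanged and equals 0.23 to 0.77 SE.

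**Step 4. Cross-check in raw correlations.** Let a be the correlation of status with T0 COPM, b its correlation with T1 COPM, and d now the raw group shift. Bias = 1.9 × d × (b − 0.5a). With a = 0.3, b = 0.4, d = 0.5, this is 1.9 × 0.5 × 0.25 = 0.24 points, in line with step 3. When b = 0.5a, status predicts T1 only through T0 COPM and the bias is zero.

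**Step 5. The both-scores rule.** Chance of a false result in favour of capability care (z above 1.96), with the same shift on both scores and an assumed correlation between the two test statistics of 0.5 to 0.7:

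| Shift | One score alone | Both scores |
|---|---|---|
| 0 | 2.5% | 0.5–0.8% |
| 0.5 SE | 7.2% | 2.0–3.1% |
| 0.69 SE | 10.2% | 3.3–4.8% |

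**Step 6. Can the sample carry one more covariate?** Residual variance falls by the factor 1 − r². The 21.7 per group becomes 20.8 (r = 0.2), 19.7 (r = 0.3) or 18.2 (r = 0.4). A 0.5 SD group difference inflates the variance of the group coefficient by about 6%, giving about 22.1, 20.9 and 19.3. All are below 24.

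**The case against.** Three stronger readings are tempting, and the documents support none of them.

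- **That any severity shift between the groups is read as a care effect.** Only the part not absorbed by T0 COPM, age, gender and diagnosis can bias the estimate. The documents give no correlation between severity and COPM, so it cannot be said that T0 COPM carries no severity information. The direction is also open.
- **That the protocol presents covariate adjustment as its protection against case-mix differences.** It gives no reason for the list as a whole. The Discussion explains only diagnosis, as cover for possible differences between the two diseases.
- **That the both-scores rule gives no protection.** Step 5 shows that it removes much of the excess. At a 0.5 SE shift the joint false-success rate is 2.0–3.1%, near the nominal one-sided 2.5% for a single score.

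Other objections also have weight. Follow-up re-scores the COPM, so self-selection of occupations may weaken the link with severity at T1 as well as at T0, and r could be small. Both groups come from one centre, with the same eligibility criteria and professionals, and no systematic shift is demonstrated. Chance imbalance (SD about √(2/30) = 0.26 at 30 per group) is already reflected in the standard error. Finally, the Discussion says that the use of SF-36 and EQ-5D in NMD needs further study, so no single instrument is the evident choice.

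These points limit the size and certainty of the concern but do not remove it. The groups are recruited in different periods, new referrals and annual check-ups are both eligible in proportions that are not fixed, and the covariate list is an explicit choice that leaves out status scores already in hand.

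**Conclusion.** The point holds as a risk of residual confounding, not as a demonstrated bias or a contradiction in the plan. Under the assumed ranges the bias is modest: about 0.10 to 0.33 points, 0.2 to 0.7 SE at 24 per group, and 7 to 24% of the 1.4-point COPM-P target. It could favour or disfavour capability care. The result rests on an assumed group difference of 0.3 to 0.5 SD and an assumed partial correlation of 0.2 to 0.4. Requiring both scores to be significant lowers the risk of false success but does not correct the estimate, because the same shift can move both scores. The change is worth making because it uses data already collected and the planned sample can carry it.

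**What to change.** In the analysis section, add one T0 health- or functional-status score to the covariates of both primary COPM ANCOVAs. Candidates collected in both groups are an SF-36 score, USER-P and the EQ-5D-5L index. Choose one on substantive grounds and name it before any capability-group T1 data are seen. The Study status section says that inclusion in that group had not begun at the time of writing. Keep the present four-covariate model as a sensitivity analysis and report both estimates.

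The cost is one sentence and no new data. The model loses one degree of freedom, the variance of the group coefficient rises slightly if the groups differ on the score (about 6% at a 0.5 SD difference, before the gain from lower residual variance), and a simple rule is needed for a patient whose T0 questionnaire is missing, such as baseline imputation.

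### The CSWQ overall question is the only listed outcome compared between the non-randomised groups without age, gender or diagnosis and without conditioning on T0, although the Discussion announces diagnosis as a covariate

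*Protocol article*

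**What the plan says.** All of the analysis text is in the protocol article, Statistical analysis, under Primary and secondary outcome measures.

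- Primary (COPM performance and satisfaction): "The primary outcome measure will be analysed using an ANCOVA model with the follow up scores (T1) as dependent variable". The adjustment set is fixed in the sentence after that: "Covariates will be the T0 scores, age, gender and diagnosis".
- Secondary: "Similar analyses (ANCOVA model) will be performed for these secondary outcome measures". Eight scores follow: two each for ICECAP-A, EQ-5D-5L and SF-36, plus USER-P and the CSWQ total score.
- The exception: "The CSWQ overall question will be analysed using a Mann-Whitney U test on the difference score between T0 and T1". It is judged at the same threshold: "A p-value below 0.05 will be considered significant". No reason, stratification or sensitivity analysis is given.

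On design, the Patient groups section states "Two patient groups are included in a controlled before and after design", and the Discussion explains that "it is not possible to randomly assign the patients to a treatment group". The Discussion also states, without naming an exception, "we decided to analyse our data using diagnosis as a covariate to take the possibility of differences into account".

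**The concern.** The article names the test for this item, so this is a stated choice and not a detail left to an unseen analysis plan. Three features of the choice are open to question.

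1. A Mann-Whitney test has no place for age, gender or diagnosis. The two cohorts are recruited one after the other, so nothing in the design balances these factors. The Discussion's commitment on diagnosis is not met for this item.
2. T0 is subtracted, not conditioned on. Every other score is conditioned on T0. The CSWQ total score and the CSWQ overall question come from one questionnaire but would be compared under different adjustment, so a disagreement between them would be hard to interpret.
3. If the item is ordinal, taking T1 minus T0 before ranking counts every one-category step as equal. That gives up much of the reason for using a rank test.

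At stake are the power and the interpretability of one secondary result.

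**Working it through.** **The plan's own figure.** No sample size or power is given for the CSWQ. The only figure is for COPM, and it reproduces. The ANCOVA residual SD is 1.9 × √(1 − 0.5²) = 1.645. For COPM-P, n = 2 × (1.96 + 0.842)² × (1.645/1.4)² = 21.7, so 22 per group by the normal approximation. By the non-central t, power is 0.805 at 23 and 0.822 at 24 per group. The stated 24 is sound and nothing below changes it. It does show that the plan relies on the efficiency of conditioning on T0 for its primary outcome.

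**Which outcomes are adjusted**

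| Outcome | Method | T0 | Age, gender, diagnosis |
|---|---|---|---|
| COPM-P, COPM-S | ANCOVA | conditioned on | yes |
| Eight secondary scores, including CSWQ total | ANCOVA, described as similar | conditioned on | yes, reading similar as the same covariates |
| CSWQ overall question | Mann-Whitney on change | subtracted | no |

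**Efficiency, by formula.** With equal variances at T0 and T1 and correlation ρ, the change score has variance proportional to 2(1 − ρ), and the T0-adjusted score to 1 − ρ². The ratio is 2/(1 + ρ):

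- ρ = 0.3: 1.40/0.91 = 1.54
- ρ = 0.5: 1.00/0.75 = 1.33
- ρ = 0.7: 0.60/0.51 = 1.18

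**Efficiency, by simulation.** The article does not give the item's number of levels, its T0-T1 correlation or an expected effect. Assumed here: 5 levels, 30 per group, a true effect of 0.7 SD, no baseline difference, two-sided 0.05. The 0.5 correlation is borrowed from the COPM calculation.

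| ρ | Mann-Whitney on change | Rank ANCOVA with T0, age, gender, diagnosis |
|---|---|---|
| 0.5 | about 64% | about 78% |
| 0.7 | about 81% | about 88% |

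This gain needs no imbalance between the cohorts. With 15 per group, rank ANCOVA still held its size.

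**Diagnosis mix.** Assumed: no treatment effect, 30 per group, ρ = 0.5, one diagnosis making up 35% of one cohort and 65% of the other, and diagnosis shifting T1 by 0.8 SD but not T0. The planned test rejects in about 12% of runs, against about 5.5% for the adjusted rank ANCOVA. With a 0.5 SD shift, the planned test rejects in about 7.3%. A diagnosis effect that was the same at T0 and T1 would largely cancel in the difference, so this result concerns effects on change.

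**A T0 difference between cohorts.** Assumed: no treatment effect, 0.5 SD difference at T0, ρ = 0.5, 30 per group.

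| Cause of the T0 difference | Mann-Whitney on change | T0-adjusted analysis |
|---|---|---|
| Both cohorts regress to a common mean | about 13% | about 5% |
| Cohorts differ by a stable amount | about 4-6% | about 19-20% |

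The ranking of the two methods reverses with the assumption.

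**The case against.** The strongest reply concerns the last table. A reader might infer that the planned test has an inflated false-positive rate whenever the cohorts differ at baseline. The documents do not support that. In non-randomised groups a T0 difference may reflect stable case mix, and then the change score is nearly unbiased while conditioning on T0 misleads (Lord's paradox). Nothing in the article says which situation applies. This objection stands in full, and the point does not rest on that claim.

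A reader might also infer that baseline is ignored, or that the article ties its covariates to the sequential design. Neither is right. T0 is subtracted, and the article gives a reason only for diagnosis: possible differences between the two diseases.

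Other replies stand in part.

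- The simulation inputs lie outside the document, so the figures are illustrative.
- A rank test on change is a recognised choice for a single item in a small sample, but the article does not give this as its reason.
- A full proportional-odds model with T0 as separate categories and three covariates can be unstable at about 15 per group. This bears on the choice of replacement.
- The article does not say that an effect estimate will be withheld, so no complaint is made about reporting.
- This is one item of one secondary questionnaire, and success is defined by COPM alone. That lowers the priority but leaves the inconsistency.

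None of this explains why age, gender and diagnosis are dropped for this item only.

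**Conclusion.** The concern holds as an inconsistency and a probable loss of efficiency in one minor secondary analysis. The omission of the three covariates, and the conflict with the Discussion's statement on diagnosis, follow from the text and need no simulation. The equal-spacing point holds if the item is ordinal, which the article does not state.

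The size is conditional. At the assumed 5 levels, 30 per group and 0.7 SD effect, the loss is about 14 percentage points of power at ρ = 0.5 (78 − 64) and about 7 at ρ = 0.7 (88 − 81). Error inflation is possible if the diagnosis mix differs and diagnosis affects change. The direction of any bias from a T0 difference cannot be settled from the document. The COPM conclusion and the sample size are unaffected.

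**What to change.** Replace the sentence on the CSWQ overall question with one prespecified model: a rank ANCOVA of T1 on group, T0, age, gender and diagnosis. Proportional-odds regression with the same covariates, and with T0 entered as one ordered score, is an acceptable alternative. Name one of the two now, so that the choice does not depend on how sparse the categories turn out to be. Keep the Mann-Whitney test on change as a sensitivity analysis. If the two disagree, their different assumptions about baseline are a possible explanation and should be discussed as such.

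The cost is a sentence, a check of model assumptions and a few degrees of freedom. The T0 score and the other covariates are already planned for the other models, so no new data are needed. According to Study status, inclusion in the capability care group had yet to start when the article was written, so at that stage the change could be fixed before any comparative data existed.

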As secondary outcome measures, we have chosen a selection of established participation (USER-P), health-related quality of life (SF-36, EQ-5D-5L) and capability outcome measures (ICECAP-A, CSWQ), to be able to obtain a broader assessment of the well-being of patients. The USER-P is a rehabilitation outcome measure that focuses on the domain of participation. The ICECAP-A and CSWQ are outcome measures developed based on the capability approach, where the ICECAP-A measures well-being in general, and the CSWQ is focused on capabilities and well-being in work. The SF-36 and EQ-5D-5L are measures of health-related quality of life (HRQoL). The SF-36 and EQ-5D have been used by HRQoL studies in NMD but its use needs further investigation [35, 36]. Especially in the context of chronic and progressive diseases, the sensitivity of SF-36 and EQ-5D to subtle changes in the condition of patients during rehabilitation is limited. Comparing the SF-36 and EQ-5D with capability-based outcome measures could provide more information on the relevance of using these instruments to assess well-being in NMD and their sensitivity to changes in the well-being of patients.

Next to using quantitative measures, we will also perform a process analysis using qualitative data. This provides us with information on what is actually happening during rehabilitation care (audio recordings of consultations with healthcare professionals and team meetings; medical records, how the patients and their partners have experienced the care (retrospective interviews with patients and if possible their partners), and how the healthcare professionals have experienced the difference between usual care and capability care (focus groups with healthcare professionals). This will help us in understanding the underlying mechanisms of usual and capability care. Comparing the quantitative outcome measures and triangulating these with the qualitative results will provide us with more insight into the effects of capability care and its critical elements.

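### The instrument comparison takes its count of patients with significant change from ANCOVA models that classify no individual patient; a separate individual-change rule should be fixed for each score version.

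*Protocol article*

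**What the plan says.** All of this is in the protocol article, under Statistical analysis, Primary and secondary outcome measures, unless another section is named.

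- The primary model: "The primary outcome measure will be analysed using an ANCOVA model with the follow up scores (T1) as dependent variable". The adjustment terms: "Covariates will be the T0 scores, age, gender and diagnosis".
- The same approach is extended to ICECAP-A, EQ-5D-5L and SF-36, among others: "Similar analyses (ANCOVA model) will be performed for these secondary outcome measures".
- The only meaning given to significance: "A p-value below 0.05 will be considered significant".
- The instrument comparison is to use contingency tables that "compare the number of patients that show significant changes in their well-being based on the ICECAP-A, EQ-5D-5L and SF-36 ANCOVA models".
- Both scorings are to be tabulated: "These comparisons will be performed both for the sum scores and the preference-weighted scores".

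The comparison serves a declared purpose. The Outcome measures section gives one reason for the broad set of measures as "to compare the validity of different instruments". The Discussion says that setting SF-36 and EQ-5D beside capability-based measures could inform on "their sensitivity to changes in the well-being of patients", and it also presents the choice of measures as a way to compare operationalisations of well-being.

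**The concern.** A contingency table of patients needs one label per patient per instrument. The ANCOVA supplies one test per instrument, and that test asks whether the two groups differ at T1 given T0 and the covariates. It does not ask whether any one patient changed. The sentence treats a group-level result as if it were an individual-level criterion.

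This is more than a detail that an article may leave to an analysis plan. Had the article said only that patients with significant change would be cross-tabulated, the threshold could properly sit elsewhere. Instead it names the ANCOVA models as the source of the classification. An analysis plan that followed the sentence would inherit the problem, and one that repaired it would depart from the article.

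At stake is the comparison of the capability measure with the health-related quality of life measures. The tables are the only quantitative method that the statistical section gives for that comparison. Which instrument looks more responsive will depend on whatever patient-level rule is put in place of the missing one.

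**Working it through.** **The plan's own figure.** The article gives no number for the instrument comparison. Its one power statement (Sample size calculation: 24 per group, 80%) concerns COPM and reproduces. The adjusted SD is 1.9 × √(1 − 0.5²) = 1.645. Noncentral-t power at 24 per group, two-sided 0.05, is 82.2% for a difference of 1.4 and 97.5% for 1.9. The product is 80.1% if the two are treated as independent. Nothing below touches it.

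**What the models deliver.** 3 instruments × 2 scorings = 6 ANCOVAs. Each gives one adjusted group difference and one p-value: 6 group-level results, 0 patient classifications.

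**Can the model's own residuals label patients?** Simulation, 2,000 trials per scenario, 30 versus 30 patients, assumed T0–T1 correlation 0.5, group, T0 score and three further covariates in the model. A patient is flagged if |studentised residual| > 1.96.

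| Assumed true effect (SD) | Patients flagged | ANCOVA power |
|---|---|---|
| 0 | 4.9% | 5% |
| 0.5 | 4.9% | 58% |
| 1.0 | 4.9% | 99% |

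The count stays constant because the fitted model already contains the group term. It says nothing about responsiveness.

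**Can another construction use the model?** Yes, with an added rule. Fit the model to usual-care patients only and flag capability-care patients above its upper 97.5% prediction limit. With r = 0.5 and estimation error ignored, the residual SD is √(1 − 0.5²) = 0.866 and the flagged share is P(Z > 1.96 − effect/0.866).

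- Effect 0: 2.5%.
- Effect 0.5 SD: P(Z > 1.383) ≈ 8%.
- Effect 1.0 SD: P(Z > 0.805) ≈ 21%.

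This count does carry information, but the rule, the reference group and the error term are not in the article.

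**How much does the choice of rule matter?** Scores are taken as normal with SD 1, and SD(change) = √(2(1 − r)). All correlations and reliabilities for these instruments are assumptions; the article gives none.

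No true change, 60 patients, changes in either direction counted:

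- Half-SD rule, r = 0.5: SD(change) = 1.000; P(|Z| > 0.50) = 0.62; about 37 of 60.
- Half-SD rule, r = 0.8: SD(change) = 0.632; P(|Z| > 0.79) = 0.43; about 26 of 60.
- Reliable-change rule, |T1 − T0| > 1.96 × √2 × SEM with SEM = SD × √(1 − reliability). If reliability equals r, the cut-off is 1.96 × SD(change), so 5%, or 3 of 60.
- Same rule, reliability 0.8 but r = 0.5: cut-off 1.96 × √2 × √0.2 = 1.24; P(|Z| > 1.24) ≈ 0.215; about 13 of 60.

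Reliable-change rule, improvement only, capability-care group, r = 0.5 (simulated):

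| Assumed reliability | Improved, true effect 0 | Improved, true effect 0.5 SD |
|---|---|---|
| 0.6 | 4% | 10% |
| 0.7 | 6% | 15% |
| 0.8 | 11% | 23% |
| 0.9 | 19% | 35% |

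**The case against.** A reader might infer that the instrument comparison cannot be run at all. The documents do not support that. Individual change scores can be built by regression from the listed covariates, and the usual-care prediction-limit version above shows that such a count can respond to a true effect. What is missing is a stated rule and error term, together with a corrected reference to the ANCOVA.

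A reader might also infer that the cut-off will be chosen after the results are seen. Nothing in the article shows this. An analysis plan may exist that was not available here, and Study status says that inclusion in the capability-care group had yet to start. There was still time to set a rule before any comparison.

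The illustrative counts deserve the same caution. The figure of 3 of 60 holds only when the reliability used equals the six-month correlation; one plausible mismatch turns it into 13. All counts out of 60 assume no dropout, although the Sample size calculation section allows for some. They show that rules disagree, not that the plan is biased towards one instrument.

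Finally, no conclusion about the effect of capability care rests on these tables. All of these objections stand. They limit the weight of the point. They do not supply the missing link, because the article still names as its source a model that labels no patient.

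**Conclusion.** The point holds in a limited form. As written, the contingency tables have no valid source: six group-level tests and no patient-level classification. This should be fixed, but it is not a flaw in the trial's main inference. It leaves untouched the COPM success rule, the sample size and the ANCOVAs as group comparisons, and no number stated in the article is wrong.

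That the models classify no patient follows from what an ANCOVA estimates and needs no numerical assumption. The size of the consequence does. The 10% to 35% range for patients called improved assumes normal scores, a 0.5 SD effect, a T0–T1 correlation of 0.5 and reliabilities between 0.6 and 0.9, none of which the article gives for these instruments.

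**What to change.** 1. Remove the reference to the ANCOVA models as the source of the patient counts.
2. Before comparative data are analysed, fix one individual-change rule, for example a reliable change index (T1 − T0 beyond 1.96 × √2 × SEM), for each of the six score versions. State the reliability value used for each and where it comes from.
3. Cross-tabulate improved versus not improved between instruments, within each scoring, and report kappa and McNemar's test. If improved, unchanged and worse are kept as three categories, McNemar does not apply; use a symmetry or marginal-homogeneity test such as Bowker or Stuart-Maxwell.
4. Optionally, add a group-level comparison: the adjusted ANCOVA effects, standardised and shown side by side, with confidence intervals from a bootstrap that resamples patients so that the pairing between instruments is kept. This says little about responsiveness if the intervention itself has little effect.
5. Use COPM change as an external anchor only if its correlation with change on these instruments is checked. COPM covers self-chosen occupations, and the article does not show that it moves with generic measures.

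The cost is analysis wording and modest programming; no new data are needed. The downside is that six reliability values must be sourced and the counts depend on them, so a sensitivity range should be reported.
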